
### Hypothesis

Based on the project Logic Model (Fig. 2), we anticipate that the RASP initiative will yield positive impacts in the short, medium, and long terms, leading to substantial changes in the capacity of mental health support and primary health care providers. Specifically, we hypothesize that RASP will result in a minimum 10% reduction in high-cost health services utilization (e.g. ED visits, mobile crisis visits, and inpatient treatments) and corresponding 10% cost savings. Additionally, we anticipate a reduction in the wait times for patient consultations with psychiatrists within the publicly funded MHAP to less than 30 calendar days. This forecast is expected to be found in both within-subject and between-subject comparisons. In addition, we hypothesize that at least 90% of patients attending the RASP will express satisfaction with the services received. Finally, we hypothesize that primary care providers and healthcare partners will express high satisfaction with RASP. These hypotheses are derived from anecdotal evidence gathered from a similar program implemented at Fort McMurray between 2013 and 2016 by the Senior Investigator.

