**Discussion:**

We expect that RASP evaluation findings will demonstrate a minimum 10% reduction in high-cost health services utilization and corresponding 10% cost savings, and also a reduction in the wait times for patient consultations with psychiatrists to less than 30 calendar days, in both within-subject and between-subject comparisons. In addition, we anticipate that patients, healthcare providers and healthcare partners would express high levels of satisfaction with the new service.

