### Rapid access and stabilization program

Nova Scotia Health (NSH) has been working to expand access to quality addiction and mental health programs through various services and technology-based health initiatives [32]. The provincial Mental Health and Addictions Program (MHAP) is delivered using the stepped care model, where a continuum of services and service providers are available to support people’s specific needs, from the least intensive interventions (health promotion, primary care, self-management, community care) to the most intensive treatment services (formal and specialized mental health & addictions care) for more complex needs [32]. To further expand capacity and access to mental health care, the province has launched a novel mental health initiative for people in need of mental health care at various intensity levels to reduce wait times for access to mental health and psychiatric support, reduce ED visits for mental health concerns and reduce inpatient psychiatric treatments.

This new service is referred to as the Rapid Access and Stabilization Program (RASP) [33], a tier 3 model of care (Fig. 1) implemented in April 2023, which aims to offer comprehensive mental health assessment, develop treatment plans, and provide short-term stabilization and mental health support to patients.

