### Study design

This is a hypothesis-driven program evaluation study that employs a mixed methods approach to evaluate the RASP. It consists of a within-subject comparison (pre- and post-evaluation study) and a controlled between-subject comparison (cohort study). The pre-and post-evaluation study will examine health services utilization data from patients attending RASP, one year before and one year after their psychiatry assessment at the program (Fig. 3a). The pre-and post-evaluation of health services utilization will also enable a comparison between RASP patients who choose to participate in the optional Text4Support RCT and those who choose not to participate in the optional Text4Support RCT.

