### Outcome measures

Primary outcome measures will include the mean differences in the frequency/duration/related costs of high-cost mental health services utilization (i.e., volume and proportion of mobile crisis visits, ED visits, hospital admissions and readmissions and associated LOS for each admission) between one year pre- and post-assessment date for same patients at RASP (within-subject comparison) and between the IG (RASP) and CG (historical data) (between-subjects comparison). Other primary outcome measures will be the mean difference in the number and proportion of total referrals booked directly for a psychiatrist and the number of calendar days for access to psychiatrists, also compared to the control group.

Secondary outcome measures include the mean difference in the frequency/duration/related costs of high-cost health services utilization one year post for patients who access the RASP and participate in the Text4Support RCT (to receive either daily supportive text messages or a single text message with a link to e-mental health resources) and patients accessing RASP but who do not participate in the Text4Support RCT. Other secondary outcome measures include a descriptive summary of the sociodemographic and clinical characteristics of the assisted population, the mean scores on the Patient Health Questionnaire 9 (PHQ-9) [38], Generalized Anxiety Disorder 7 (GAD-7) [39], World Health Organization 5 (WHO 5 Well-Being Index) [40], Brief Resilience Scale (BRS) [41], Recovery Assessment Scale (RAS) [42], Adverse Childhood Experience (ACE questionnaire) [43], Brief Substance use Craving Scale (BSCS) [44], and the Columbia-suicide severity rating scale (C-SSRS) [45], as well as the prevalence of likely MDD, GAD and low resilience. Patient overall impressions (i.e. barriers to accessing RASP, satisfaction level, likely recommend the service to others, etc.) and impressions on the experience (i.e. feelings of welcomeness, respect, enough time to talk, the problem addressed, and understanding of treatment) are part of the patient satisfaction quantitative evaluation. An in-depth evaluation of healthcare partner impressions and patient satisfaction will be obtained through qualitative key informant interviews until saturation is reached and no new themes and subthemes emerge.

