### Data analysis

#### Quantitative analysis

Quantitative data will be analyzed using descriptive and inferential statistics by using SPSS version 26 for Windows [46]. First, we will summarize the study participants' sociodemographic and clinical descriptive characteristics. Primary outcomes comparing the pre-and post-enrollment health services utilization for patients accessing RASP will be analyzed using descriptive and inferential statistical analysis, including Chi-Square and independent sample t-tests. For the primary outcome involving control populations, pre- and post-enrollment health services utilization variables will initially be compared using an analysis of covariance (ANCOVA) with the intervention condition (attended RASP) as the independent variable, the relevant health services utilization data one year pre attendance of appointment with RASP psychiatrist or community mental clinician as the covariate, and the relevant high-cost health services utilization data one year post attendance of appointment with a RASP psychiatrist or attendance with mental health clinicians in the community mental health program as the dependent variable. In each case, checks would be conducted to ensure no violation of regression slopes and reliable measurement of the covariate. We will perform sensitivity analyses of covariance to explore the impact of the imputation of data loss at each time point on health services utilization. In addition, we will perform propensity score matching and regression analyses adjusting for the periods pre-, during and post COVID-19 pandemic in order to strengthen the comparability of the groups and enhance the validity of the study's findings.

We will also use an ANCOVA to compare high-cost health services utilization data for one-year pre- and post-RASP attendance for the subset of patients who attend RASP and either participate or do not participate in the Text4Support RCT. For this analysis, the intervention condition (participants in the Text4Support RCT) will be the independent variable, the relevant health services utilization data one-year pre-attendance of appointment with RASP psychiatrist will be the covariate, and the relevant high-cost health services utilization data one-year post attendance of appointment with a RASP psychiatrist will be the dependent variable.

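### The 10% reduction hypothesis is also applied, as a primary outcome, to an uncontrolled pre/post change that regression to the mean could produce in part or in whole

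*Protocol article*

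**What the plan says.** The Hypothesis section states that "we hypothesize that RASP will result in a minimum 10% reduction in high-cost health services utilization", with cost savings of the same size, and then that "This forecast is expected to be found in both within-subject and between-subject comparisons". Read alone, that sentence could refer only to the waiting-time forecast just before it. The Discussion paragraph of the abstract removes the doubt: it lists utilisation, cost and waiting time together and ends "in both within-subject and between-subject comparisons".

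Under Outcome measures, the primary outcomes include the mean difference in frequency, duration and related costs "between one year pre- and post-assessment date for same patients at RASP (within-subject comparison", alongside the comparison with historical controls. Study design sets the windows at "one year before and one year after their psychiatry assessment at the program".

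Under Quantitative analysis, the pre/post outcomes "will be analyzed using descriptive and inferential statistical analysis, including Chi-Square and independent sample t-tests". ANCOVA on pre-year use is described for the comparison with controls (and for the Text4Support subset). Propensity score matching and adjustment for pandemic period are added to make the groups more comparable.

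On entry, the section on the programme describes a service "for people in need of mental health care at various intensity levels". Primary care providers refer through central intake, and no threshold on past high-cost use is given. The Hypothesis section anticipates "a reduction in the wait times for patient consultations with psychiatrists within the publicly funded MHAP to less than 30 calendar days".

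**The concern.** Patients are referred because of a current need. The pre-year ends at the RASP assessment and the anticipated wait is under 30 days, so the need that prompted referral normally lies inside the pre-year. If recent ED, crisis or inpatient use makes referral more likely, the pre-year is elevated on average. The next year then drifts back towards the long-run level whether or not the programme does anything.

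The within-subject test compares the two years with no comparator, so it cannot separate this drift from a programme effect. With about 2500 patients even a modest drift can be statistically significant. What is at stake is a statement that the 10% utilisation or cost hypothesis was met within subjects, taken as evidence that RASP works.

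**Working it through.** **The plan's own figure.** The only sample size given is for the between-group comparison: 525 per group, from a control mean of 10, SD 1, a 10% reduction (1 unit), 90% power and two-sided alpha 0.05. With n = 2(1.960 + 1.282)² × SD²/1², SD = 1 gives 21.0, so 22 per group. SD = 5 gives 525.4, so 526, which matches. The inconsistency is a separate point. It matters here because the spread of utilisation affects how easily a 10% artefact arises.

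**Formula.** Set the long-run mean to 1. Let k be the pre-year mean of referred patients relative to it, and rho the year-to-year correlation. With no programme effect the post-year mean is 1 + rho(k - 1), so

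fall = [k - 1 - rho(k - 1)]/k = (1 - rho)(1 - 1/k).

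The article gives neither k nor rho. Both are assumptions, so the whole grid is shown:

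| k | rho = 0.3 | rho = 0.5 | rho = 0.7 | rho = 0.9 |
|---|---|---|---|---|
| 1.25 | 14% | 10% | 6% | 2% |
| 1.5 | 23% | 17% | 10% | 3% |
| 2 | 35% | 25% | 15% | 5% |

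At k = 1 (referral unrelated to recent use) every entry is 0%.

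**On the plan's scale.** With a pre-year mean of 10, a null fall of 1 unit needs an entry elevation of 1/(1 - rho) units: 1.43, 2.0, 3.33 and 10 at rho = 0.3, 0.5, 0.7 and 0.9.
- With SD = 5 (the value that reproduces 525) this is 0.29, 0.40, 0.67 and 2.0 SD.
- With SD = 1 as printed it is 1.43, 2.0, 3.33 and 10 SD.
- Conversely, an entry mean 0.5 SD above the long-run mean gives falls of 17.5%, 12.5%, 7.5% and 2.5% with SD = 5, but only 3.5%, 2.5%, 1.5% and 0.5% with SD = 1.

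**Event view.** Suppose a share f of patients had one extra event that prompted referral, on top of a usual mean of mu per year. The null fall is f/(mu + f), which is 10% when f = mu/9: 5.6% of patients at mu = 0.5, 11% at mu = 1, 22% at mu = 2, and all patients at mu = 9.

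**Simulation under no effect.** Counts were gamma-Poisson with identical individual rates in both years. Referral probability was proportional to 1 + w × pre-year events. An independent-sample t-test was applied to 200 samples of 2500 per setting.

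| mu | w = 0 | w = 0.1 | w = 0.3 | w = 1.0 |
|---|---|---|---|---|
| 0.5 | 0% | 7.8% | 17.5% | 28.6% |
| 1 | 0% | 7.2% | 13.5% | 20.6% |
| 2 | 0% | 6.1% | 9.3% | 12.5% |
| 10 (SD about 5.7) | 0% | 4.2% | 6.1% | 6.8% |
| 10 (SD about 3.2) | 0% | 4.7% | 7.0% | 8.4% |

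The fall was significant in 95% to 100% of samples when w was 0.3 or more. At w = 0.1 it was significant in 14% to 29% of samples for mu of 0.5 to 2, and in 91% to 100% for mu = 10.

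So 10% is easily reached at low, skewed event rates. It was not reached in any simulated setting at a mean of 10, although smaller null falls there were still usually significant when referral depended on recent use.

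**The case against.** The case on the other side is substantial.

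- **The forecast is a joint one.** The Hypothesis section expects the fall in both comparisons, so read literally a pre/post fall alone does not satisfy it. Study design gives the question of association with RASP to the controlled cohort. Only that comparison has ANCOVA with controls, matching and a power calculation. A reader might infer that the two comparisons stand on an equal footing; the documents do not say that.
- **Costs are controlled.** A reader might infer that the cost-saving claim rests on the pre/post fall. The Health economic evaluation section compares outcomes and costs with the control group. Only the within-subject cost outcome listed under Outcome measures is exposed.
- **The size is not established.** A reader might infer that the within-subject hypothesis would probably be met whether or not RASP works. The documents do not support that. Entry is by referral, not by a threshold on past use, and the abstract describes care that does not require ED visits or hospitalisation. Being unwell at referral need not mean an elevated count of high-cost events. Patients at acute risk are transferred to the ED at assessment, which may add post-year events.

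All of this limits the consequence. It does not remove the point: the within-subject change remains a primary outcome with its own uncontrolled test and carries the same 10% forecast. The controlled analysis cannot protect a conclusion drawn from that result.

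**Conclusion.** The point holds as a bias of unknown size in one of the two primary comparisons. Regression to the mean could yield part or all of a 10% within-subject fall with no programme effect: about 2% at k = 1.25 and rho = 0.9, 10% at k = 1.25 and rho = 0.5, 25% at k = 2 and rho = 0.5, and zero if referral is unrelated to recent use. These figures rest on assumed k and rho. They show that a 10% fall is possible under no effect, not that it is likely. Because the size is unknown, an uncontrolled change cannot confirm a 10% effect. The change should be made, and it is small, because the article already plans the controlled analysis that is needed.

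**What to change.** 1. In Hypothesis and Outcome measures (and the abstract), state that the 10% utilisation and cost hypotheses are judged on the controlled comparison.
2. Name the ANCOVA already described under Quantitative analysis as the single primary estimator, with the difference in pre/post change as a sensitivity analysis. The two are not interchangeable in non-randomised groups: they differ by (1 - b) times the baseline difference, where b is the ANCOVA slope. With b = 0.5 (assumed) and a baseline imbalance of 20% of the mean, the gap is 0.5 × 20% = 10% of the mean, as large as the hypothesised effect.
3. Report the RASP pre/post change as descriptive, beside the control group's change over windows with the same anchor.
4. Reconcile the anchor. Sample size considerations counts one year after initial referral; Quantitative analysis counts from the appointment attended. Controls were waitlisted first, so with appointment anchoring the drift may differ between groups even within the ANCOVA.
5. Optionally, add a sensitivity analysis that excludes the months just before the anchor in both groups, expressed as rates per unit time so that the unequal windows stay comparable.

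The cost is mainly wording, since pre- and post-year data are already planned for both groups. Settling the anchor may change the extraction windows, and item 5 adds one analysis. The downside is that the pre/post figure loses confirmatory status.

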**Fig. 2 Fig2:**
[figure not shown]
Logic Model for the RASP

### Study design

This is a hypothesis-driven program evaluation study that employs a mixed methods approach to evaluate the RASP. It consists of a within-subject comparison (pre- and post-evaluation study) and a controlled between-subject comparison (cohort study). The pre-and post-evaluation study will examine health services utilization data from patients attending RASP, one year before and one year after their psychiatry assessment at the program (Fig. 3a). The pre-and post-evaluation of health services utilization will also enable a comparison between RASP patients who choose to participate in the optional Text4Support RCT and those who choose not to participate in the optional Text4Support RCT.

**Fig. 3 Fig3:**
[figure not shown]
Study design diagram (**a** Pre-and post-evaluation study; **b** Controlled cohort study)

The cohort study will compare two study populations: the intervention group (IG) consisting of patients attending RASP, and the control group (CG), comprising a cohort of patients who were referred by PHP to the MHAP central intake services prior to RASP implementation (Fig. 3b). This design allows researchers to examine whether possible changes in high-cost health services utilization are associated with the intervention (RASP).

A cross-sectional evaluation of mental health outcomes at program entry will be employed to evaluate the prevalence and correlates of the various psychological conditions of the assisted population.

Patient experience and satisfaction will be assessed using both quantitative and qualitative data. The quantitative data will be extracted from the program's satisfaction survey, while the qualitative data will be gathered from a purposive sub-sample of the overall study population. The selected sub-sample will be invited to participate in focus group discussions as part of a sub-study to gain deeper insights into their experiences and perspectives. Key informant interviews will be conducted to obtain qualitative insights from various healthcare partners, including directors, psychiatrists, primary healthcare providers, MHA service leaders, and community organizations. These interviews will focus on their perceptions regarding the impact of RASP on patients' access to community mental health care and the support it provides for primary care providers. Qualitative descriptive methodology and thematic analysis will be employed to generate and refine the information and identify patterns or themes within the qualitative data [35, 36]. This research protocol has been approved by the Research Ethics Board at Nova Scotia Health (REB file #1028254). The Gantt chart timeline is presented in the supplementary material (Table S1).

### Participants and data collection

All RASP patients receive a consent form as part of their intake process, allowing access to their health services utilization records. Only those who sign the consent form will be part of the study. While consent is obtained during the initial assessment for ongoing patient recruitment, data collection is scheduled to commence after the program's first year, in April 2024. Service utilization data will extracted from provincial information systems retrospectively and prospectively at 2-time points: one year pre- and one-year post-assessment date at RASP. In addition, sociodemographic and mental health assessment information, including results from patient-completed validated scales and psychiatry diagnosis, and patient satisfaction will be extracted from routine paper-based initial screening forms. Patient satisfaction quantitative data will be extracted from RASP's patient satisfaction survey, available in a paper-based format and completed immediately after the assessment or REDCap online survey link sent via text message to all patients attending the service just after the assessment appointment.

The control group for the cohort study will comprise patients referred to the MHAP Central Intake Services by a PHP before RASP implementation. The periods for inclusion in the control group will be May 2017 to May 2019 (pre-COVID) and May 2020 to May 2022 (during COVID). By examining the data from these two time points (pre-COVID and during COVID) and comparing them with each other and with data during the RASP implementation period, we will be able to evaluate the impact of the pandemic on health services utilization as well as the impact of RASP implementation in comparison with both the pre-pandemic and during the pandemic periods. Ethics approval for exemption from requiring informed consent for all control group patients has been granted by the Research Ethics Board at Nova Scotia Health (REB file #1028254), allowing control group patients' sociodemographic and health services utilization information from provincial administrative databases to be accessed by the investigators.

For the qualitative component of the study, expected to take place after a year of RASP implementation, in April 2024, a sub-sample from the overall pool of the intervention population (RASP patients) will be invited by a research team member to participate in a focus group session. The inclusion criteria to participate in the qualitative sub-study are to provide consent and be available to attend a 1-hour focus group session, which will be audio-recorded. The focus group script will be developed by investigators, reviewed by healthcare partners, piloted with patients and adjusted as needed, before being used in the focus groups. A trained research team member will conduct the encounters, which may happen in person or via Zoom. The sample size for the qualitative component of the study cannot be predetermined because data saturation needs to be reached. Data analysis ends when no new themes and subthemes emerge across all analysts. However, based on what the literature suggests [37], we anticipate that 25-30 participants may be sufficient for this mixed-methods study. Participants will receive compensation for their time spent participating in the qualitative sub-study activities.

Healthcare partners involved with RASP will be also actively engaged in the qualitative evaluation of the program. Trained members of the research team will conduct individual key informant interviews, either virtually or in person, with program directors, psychiatrists, primary healthcare providers, MHA service leaders, and representatives from community organizations. These interviews aim to gather in-depth information about healthcare partners' experiences and opinions regarding the program, allowing for a comprehensive understanding of their perspectives.

Finally, a sub-population of RASP patients who opted to participate in the Text4Support RCT will also have their one-year pre- and post-RASP attendance health services utilization data collected and compared to patients who chose not to participate in the optional Text4Support RCT. RASP was launched in April 2023, with data collection ongoing. Table S2 demonstrates in detail the variables, sources and data collection time points.

